### Analysis

Statistical analysis will be undertaken using IBM SPSS Statistics 20 and MLwiN 2.28. The primary outcome of interest is the efficacy of the Option Grids in terms of facilitating SDM, to be measured using the Observer OPTION Scale [20]. Pre and post-intervention Observer OPTION scores will be assessed using multilevel modelling, where the patient will be the first level and the physiotherapist will be second level. Secondary analysis of the DQM, using multilevel modelling, will be used to compare whether the intervention improves knowledge and improves the ability to make a choice. The treatment decision will be assessed to compare post-intervention to pre-intervention sample. Data on age, gender, educational level, employment status and language and the REALM-R score will provide information on the socio-demographic profile of study participants as well as the extent to which they are considered to be at risk of poor health literacy. The pain severity score will provide information about the trial population and allow the identification of associations between trial outcomes and pain severity of its participants as a potential effect modifier.

Observation notes, patient, interpreter and physiotherapist interview data will be transcribed and analysed using critical discourse analysis, supported by qualitative data analysis software NVIVO version 10, to explore views on the consultation, perceptions of involvement in decision making and the use of the Option Grid. Using a coding framework, one member of the research team will code all interview data, and another will dual code a 30% sample of interviews. A sample of audio-recorded consultations purposefully sampled on the basis of a range of Option Scores and REALM-R scores will be selected for transcription and will be studied in more detail using discourse analysis. Discourse analysis is particularly suited to the analysis of dialogue in a social interaction (physiotherapist-patient consultation). It allows researchers to interpret the meanings that people ascribe to the words they use, to expose identities and the inconsistencies and inequalities within social relationships [25].

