**Methods/Design:**

This will be a stepped wedge exploratory trial involving 72 patients with OA of the knee referred from primary medical care to a specialist musculoskeletal service in Oldham. Six physiotherapists will sequentially join the trial and consult with six patients using usual care procedures. After a period of brief training in using the Option Grid, the same six physiotherapists will consult with six further patients using an Option Grid in the consultation. The primary outcome will be efficacy of the Option Grid in facilitating SDM as measured by observational scores using the OPTION scale. Comparisons will be made between patients who have received the Option Grid and those who received usual care. A Decision Quality Measure (DQM) will assess quality of decision making. The health literacy of patients will be measured using the REALM-R instrument. Consultations will be observed and audio-recorded. Interviews will be conducted with the physiotherapists, patients and any interpreters present to explore their views of using the Option Grid.

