### Sample size

10,000 new patient referrals a year are received by PMSK Ltd and it is estimated that 12-18 patients per month will present with OA of the knee which requires consideration of treatment options. Based on previous studies, the anticipated mean and standard deviation (SD) for the OPTION score are 16.9 and 7.7. Assuming that the effect of the intervention is to increase the mean by 50% and that the SD remains unaltered (the distribution simply shifts upwards) then the mean will increase to 25.35. With 36 patients (6 physiotherapists consulting 6 patients each) pre-intervention and 36 patient post-intervention, the expected value of *t* is 4.66 Adjusting for the clustering effect at the level of the physiotherapist (intra-cluster correlation = 0.22) results in a variance inflation factor (design effect) of 2.1, therefore the expected value of *t* changes to 3.22. This corresponds to a power, using this sample of 72 patients, of roughly 90% to detect a difference of this size. A 40% consent rate is estimated, requiring a population of 180 eligible patients to be contacted in order to obtain a sample of 72 patients. A conservative data collection phase of 18 months via a stepped wedge design is planned.

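### The sample size and the primary model rest on opposite clustering assumptions, and no usual choice of random terms makes both right

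*Protocol article*

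**What the plan says.** All references are to the protocol article.

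- **Design.** In the abstract (Methods/Design), after a usual-care phase and brief training, "the same six physiotherapists will consult with six further patients using an Option Grid in the consultation". Each physiotherapist therefore contributes to both sides of the comparison.
- **Sample size.** The inputs are that "the anticipated mean and standard deviation (SD) for the OPTION score are 16.9 and 7.7" and, after a 50% rise, "then the mean will increase to 25.35". The numbers are set out as "With 36 patients (6 physiotherapists consulting 6 patients each) pre-intervention and 36 patient post-intervention". The clustering allowance reads "intra-cluster correlation = 0.22) results in a variance inflation factor (design effect) of 2.1". It takes the expected t from 4.66 to 3.22 and gives a power of roughly 90%. Neither the significance level nor a between-phase correlation is stated.
- **Analysis.** The primary outcome is to be analysed by multilevel modelling, "where the patient will be the first level and the physiotherapist will be second level". The levels are fixed. Whether level 2 carries only a random intercept or also a varying phase effect is not stated. The same approach extends to the DQM: "Secondary analysis of the DQM, using multilevel modelling, will be used to compare whether the intervention improves knowledge".

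**The concern.** In a within-physiotherapist comparison, how far clustering inflates the variance depends on how much of the physiotherapist effect is shared by the two phases. What is shared cancels from the difference, and what is specific to a phase does not.

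The design effect in the Sample size section treats nothing as shared. A model with patients nested in physiotherapists and only a random intercept treats everything as shared, and tests the phase effect against patient-level variation on about 65 degrees of freedom. If there is phase-specific variation and the model omits it, confidence intervals are too narrow and p-values too small for the primary outcome, and for the DQM if it is modelled in the same way. If there is none, the clustering allowance in the sample size is wrong in the other direction. The stake is the trial's main efficacy claim and its stated power.

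**Working it through.** **Inputs.** From Sample size: SD 7.7; difference 25.35 − 16.9 = 8.45; ICC 0.22; 6 physiotherapists × 2 phases × 6 patients = 72. Assumed: two-sided 5% test, since the level is not stated (it reproduces the stated power; one-sided 5% would give 94.2%), and no time trend. Let r be the between-phase correlation of the physiotherapist effect, that is, the share of it common to both phases. The article gives no value, so the range 0 to 1 is shown.

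**1. The plan's own figure**

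- t = 8.45 / (7.7 × √(2/36)) = 8.45 / 1.815 = 4.66
- Design effect = 1 + (6 − 1) × 0.22 = 2.10
- t after inflation = 4.656 / √2.10 = 3.21 (stated 3.22)
- Power = Φ(3.21 − 1.96) = 89.5%

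The stated figure reproduces, with a cluster size of 6: one physiotherapist in one phase.

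**2. What 2.1 implies.** The true variance of the before-after difference is

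(2/36) × 7.7² × [(1 − 0.22) + 6 × 0.22 × (1 − r)]

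The bracket is 0.78 + 1.32 = 2.10 only at r = 0. At r = 1 it is 0.78.

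**3. What a random-intercept model reports.** It pools the 5 physiotherapist-by-phase degrees of freedom with the 60 patient-level ones, so its variance is about

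(2/36) × 7.7² × [(1 − 0.22) + (30/65) × 0.22 × (1 − r)]

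At r = 0 the bracket is 0.78 + 0.10 = 0.88. The true SE is 2.63 and the reported SE about 1.70, so the SE is understated 2.63 / 1.70 = 1.54-fold.

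**4. Type I error and power.** Type I error comes from simulating the balanced design (200,000 runs per setting, random intercept by REML, Wald test at 1.96). Power is for 8.45 points with the true SE and t on 5 df (critical value 2.571).

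| r | True SE | Reported SE | Type I error, random intercept | 8.45 / true SE | Power, 5 df |
|---|---|---|---|---|---|
| 1 | 1.60 | 1.60 | 5.4% | 5.27 | 98% |
| 0.8 | 1.85 | 1.62 | 9.0% | 4.56 | 95% |
| 0.5 | 2.18 | 1.65 | 14.1% | 3.88 | 87% |
| 0 | 2.63 | 1.70 | 21.0% | 3.21 | 73% |

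Maximum likelihood adds 0.2 to 0.4 points to the error rates. A t reference on 65 df gives 5.0% at r = 1 and 20.1% at r = 0. With physiotherapist-by-phase variation in the error term and t on 5 df, type I error is 5.0% at every r.

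**5. Can both sections be right?**

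- Random intercept, r = 1: the test is valid, but the 2.1 inflation does not apply.
- Random intercept, r = 0: the 2.1 is right, but type I error is about 21%.
- Random phase effect with a normal reference: six differences give 5 df, and P(|t₅| > 1.96) is about 10.7%.
- Random phase effect with t on 5 df: the test is valid, but power under the plan's own design effect is 73%.

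**The case against.** The strongest reply is that the Analysis section names levels, not random terms. A random phase coefficient at level 2 is also a two-level model with exactly those levels, and a journal article may leave such detail to the full protocol or analysis plan. That stands: the article does not commit the trial to the faulty version. It does not dispose of the point, because step 5 shows that each usual choice leaves either the test or the sample-size statement wrong.

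Second, the usual design-effect formula may be a conservative shortcut that ignores the pairing, not a belief that nothing is shared between phases. That is possible. If the physiotherapist effect is stable, the random-intercept model holds its level and the sample size errs on the safe side. The article does not say which is true.

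Third, differing uptake of a 30-minute training adds no variance if the intervention affects no physiotherapist at all. Under that strict null, inflation needs each physiotherapist to drift differently between phases. This also stands. Uptake differences bear on the interval width when generalising beyond these six, and on error under a null where individual effects average to zero.

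A reader might also infer that having only six physiotherapists causes the inflation. It does not: with the same six the error is 5.4% when r = 1. The omitted variance component is the cause. The small number limits the degrees of freedom of the remedy.

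**Conclusion.** The inconsistency is established: the Sample size section requires r = 0, and the usual reading of the Analysis section requires r = 1. If the first is right and the model has only a random intercept, type I error is about 21% and the SE is understated about 1.5-fold.

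It would be too strong to say that the planned standard error is too small, or that the error rate is 9% to 21%. Both need phase-specific variation that the article does not quantify, and the 9% end rests on an assumed r of 0.8. At r = 1 there is no inflation beyond about 5%. The results also rest on a two-sided 5% level, ICC 0.22, balanced numbers and no time trend. The firm conclusion is that roughly 90% power and a valid test do not hold together under the plan's own design effect. The valid 5-df test has 73%.

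**What to change.** - **Primary model.** Specify a physiotherapist-by-phase term, or a random phase coefficient at level 2, fitted by REML with a small-sample t reference (Satterthwaite or Kenward-Roger, about 5 df).
- **Check.** Report a paired t test on the six physiotherapist-level before-after differences (5 df).
- **DQM.** Use the same structure. I would not extend it to a random-phase logistic model for the treatment decision, which may be barely estimable with 72 patients and six clusters.
- **Sample size.** State the significance level, the assumed between-phase correlation and the power on 5 df: 73% at 0, 87% at 0.5, 95% at 0.8 and 98% at 1.

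Permuting the start times is not a substitute. Each physiotherapist sees control patients first and intervention patients second whatever the start time, so the simple before-after contrast does not change.

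The cost is wider intervals and, under the plan's own design effect, a lower stated power. No extra patients or data are needed to make the change, although the sponsor may wish to reconsider the sample size once the power is restated.

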### Ethical approval

The study protocol was approved by the South East Wales Research Ethics Committee (11/WA/0356). Written participant information about trial objectives and procedures will be given to eligible patients. Standard forms are used to document informed consent.

## Discussion

This trial will be the first to determine the efficacy of an Option Grid on facilitating shared decision making in day-to-day clinical encounters. If the intervention is found to facilitate shared decision making it will make a significant contribution to knowledge about how to promote SDM and overcome the implementation barriers experienced to date [7].

## Abbreviations

DQM: Decision quality measure; OA of the knee: Osteoarthritis of the knee; PMSK: Pennine musculoskeletal partnership Ltd; SDM: Shared decision making.
